### Participants

Participants in the study are children with a best estimate clinical DSM-IV-TR diagnosis of ASD, including Autistic disorder, Asperger’s disorder, or PDD-NOS, assigned in a multidisciplinary team including a child psychiatrist and psychologist. The diagnostic procedure consisted of an interview with parents on the current behavior and on developmental history of the child and observation of the child in a standardized, playful situation (most often the ADOS). For inclusion in the study, the Autism Diagnostic Interview-Revised (ADI-R [26]; Dutch version [27]) and the Autism Diagnostic Observation Schedule (ADOS [28]; Dutch version [29]) were administered. Participants had been referred to one of the four participating child mental health care centers. Their clinician advised them to participate in a social skills training. Motivation of the child and parents for training is established. Their IQ is above 80, they are in the last two and a half years of primary education and 10 to 12 years old.

Children with a physical condition that hampers participation or who cannot arrange visiting the child mental health center for the training have been excluded from participation. However, medication or co-morbid disorders were no reason for exclusion.

### Informed consent

When an SST was indicated, the therapist introduced this form of treatment to the parents and children and informed them about the study. Sometimes, parents or children were the ones who expressed interest in participating in a social skills training. In that case, the therapist discussed the appropriateness with parents and child and then introduced the study. If parents and children were interested in participating, they agreed that the research team would call them to give more detailed information and would send written information. When the parents and children understood the information from the researchers and were willing to participate, an appointment was scheduled with a therapist. The therapist assessed whether SST was indeed appropriate for the child and the child and parent had the chance to receive more information on the training. If parents, child, and therapist agreed on the appropriateness of treatment and participation in the RCT, the informed consent form was signed by the parents and the child, if aged 12. The researcher informed the teacher and asked for participation after parents had agreed on doing so and the teacher signed informed consent as well. All participants had the right to withdraw from the study at any time, without explanation. Refraining from the study would not affect regular treatment at the child mental health centers. Figure 1 is a flowchart with the phases of the research procedure.

**Figure 1 F1:**
[figure not shown]
Flow chart of the phases of the RCT.

### Therapists

All therapists participating in this study were psychologists who worked at one of the child mental health centers. Two therapists led one group of four to six children. At least one of the (child) psychologists had finished an additional postmaster clinical training. The other had at least a master in Psychology. Both had experience in the broader treatment of children with ASDs and had received training in the theoretical backgrounds and application of cognitive behavioral therapy. Before applying the SST, all therapists participated in a training in the specific protocol. This training lasted six hours for groups of trainers or two hours individually. Trainers received the protocol with all sessions and preparation guidelines. The training focused on the theoretical background, the manualized protocol, the content of the sessions, the physical context of the sessions, the importance of adherence to the protocol, and to the study requirements in general. During the intervention period, therapists had brief meetings or phone calls to discuss the progress of the children or the difficulties in the ongoing groups. These sessions had also been set up to enhance treatment adherence and to prevent therapists to drift from the protocol. In the beginning of the intervention, these meetings were planned weekly, later they were planned once every two weeks. One of the senior therapists of this specific SST supervised these sessions and carefully watched over treatment adherence.

### Randomization

The RCT contains three conditions: SST, SST-PTI, and care-as-usual. As soon as 4–6 children in a treatment center had finished the pretreatment assessment, that group was randomized to one of these three conditions. We used a randomized block design with blocks of 5 with a 2-2-1 ratio (2 SST, 2 SST-PTI, 1 CAU). This balanced randomization procedure was used, striving for unbiased comparison groups, but also for comparison groups of about the same size throughout the trial. The training groups were embedded in three treatment locations that have specific characteristics (Accare Groningen; ATN Groningen; Drachten [including ATN and Accare]). Therefore, we stratified the randomization by the three treatment locations. Research assistants logged in to a web-based program, that allocated groups to treatment condition (randomized on group-level in blocks of 5, stratified per treatment location).

During the inclusion period, the recruiting team was blind to the exact details of the randomization process. To conceal the predictability of the randomization process, research assistants not only entered the treatment location, but also information on the sex of the participants and the number of children in each group (4–6). Sex and group size were in fact not weighed in the randomization.

Randomization took place after all measures of the first assessment were completed. Thus, pre-treatment assessments are independent of the participant’s knowledge of treatment condition.

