### Sample size calculation

We computed the minimally required sample sizes for two repeated-measures (RM-)ANOVAs on the primary outcome measure VABS, with one between-subject factor (group; 2 levels) and one within-subject factor (time; 2 levels: T3 versus T1); in one test, the SST and care-as-usual groups will be compared and in the other the SST and SST-PTI groups. For each test, we required a power of .99, a significance level of .01, and assumed a correlation between repeated measures of the VABS of .5. Calculations were performed with the program G*Power 3.1.7 [33].

The expected difference between the SST and the care-as-usual group is based on the results of the study into SST of Owens et al. [34], who found a difference between the treated and untreated group of 0.90 SD of the mean VABS outcome. Assuming no effect in the untreated group, the associated effect size f = .4, yielding a minimal sample size of 21 per group. We expect that comparing the two treatment conditions yields lower values of difference. No literature on the comparison of two SST training conditions was available, therefore we defined the difference to detect based on clinical relevance of a difference found. This resulted in a difference between SST and SST-PTI of 0.60 SD of the mean VABS outcome, with associated effect size f = .3, yielding a minimal sample size of 36 per group. Based on our experiences in past research, we presumed a drop-out rate of 10%, implying a minimal sample size of 21/.9 = 24 children in the care-as-usual condition and 36/.9 = 40 in each of the treatment conditions. Because we could include more children in the treatment groups, yielding an even larger power, we aimed 48 in each of the treatment conditions and 24 children in the care-as-usual group (total n = 120).

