### Statistical analyses

First, the three groups will be compared with respect to background, age, IQ, and other data in order to assess the comparability between them.

Second, intervention efficacy will be established with hierarchical linear modeling. All data will be analyzed using the intent-to-treat principle. The comparative efficacies of SST, SST-PTI, and care as usual will be investigated with hierarchical linear modeling. The first will test the primary outcome, the socialization domain of the VABS. The other multilevel analyses will be done on each secondary outcome, including 1) parent reported training-specific social skills and 2) more general social skills pertaining to home and community settings, reported by parents and 3) more general social skills pertaining to home and community settings, reported by teacher.

Third, in the completers, the same analyses will be applied, while taking into account possible drop-out and treatment non-adherence. The possible mediators and moderators will be included as explanatory variables into the hierarchical linear models.

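### Whole groups of 4–6 children are randomized, but the sample size treats children as independent, so the stated .99 power is not supported; the analysis section should name the randomized group as a level

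*Protocol article*

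**What the plan says.** The Randomization section is explicit about the unit: "As soon as 4–6 children in a treatment center had finished the pretreatment assessment, that group was randomized to one of these three conditions". The program "allocated groups to treatment condition (randomized on group-level in blocks of 5, stratified per treatment location", in "blocks of 5 with a 2-2-1 ratio (2 SST, 2 SST-PTI, 1 CAU". In the training arms the group is also the treatment unit: "Two therapists led one group of four to six children" (Therapists).

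The Sample size calculation section uses an ANOVA "with one between-subject factor (group; 2 levels) and one within-subject factor (time; 2 levels: T3 versus T1". There, group means treatment arm. It states: "we required a power of .99, a significance level of .01, and assumed a correlation between repeated measures of the VABS of .5". For SST against care-as-usual it gives "the associated effect size f = .4, yielding a minimal sample size of 21 per group"; for SST against SST-PTI it gives f = .3 and 36 per group. Planned enrolment is 48, 48 and 24 children. No ICC, design effect or number of groups appears.

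The Statistical analyses section says: "The comparative efficacies of SST, SST-PTI, and care as usual will be investigated with hierarchical linear modeling". It does not name the levels. The Strengths and limitations section describes the random assignment as one of children, which does not match the Randomization section.

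**The concern.** When intact groups are randomized, the evidence about a treatment contrast comes from differences between groups. Children in one training group share two therapists and 18 sessions, and every randomized group shares a location and a recruitment period. If their changes on the Vineland Socialization domain are correlated, the effective number of children is smaller than the count, and the degrees of freedom for the contrast follow the number of groups.

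Two things are at stake. The printed power belongs to an individually randomized design, which this trial is not. More important is the primary test: the main aim compares SST with care-as-usual, which has only about five groups. A model with time within child and nothing above it would meet the words used for the analysis, yet would give standard errors that are too small.

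**Working it through.** **1. Number of groups.** Training arms: 48/6 = 8 to 48/4 = 12 each. Care-as-usual: 24/6 = 4 to 24/4 = 6. At 5 per group: 9.6, 9.6 and 4.8, taken below as 10, 10 and 5. The document gives no actual count, so the resulting degrees of freedom (10 + 5 − 2 = 13 and 10 + 10 − 2 = 18) are approximate.

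**2. Reproducing the plan's figures.** Inputs: f = .4 and .3, alpha .01, correlation .5, two time points, independent children. Within-between interaction: λ = f² × N × 2/(1 − .5), on 1 and N − 2 df.
- f = .4, N = 42: λ = .16 × 42 × 4 = 26.88, power .9915.
- f = .3, N = 72: λ = .09 × 72 × 4 = 25.92, power .9916.

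Dividing by .9 gives 24 and 40. The stated figures reproduce exactly, so no clustering allowance is hidden in them.

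**3. Power at the stated minimum sizes, with clustering.** Design effect DE = 1 + (5 − 1) × ICC, and λ is divided by DE. Child-level df are kept, which is generous. The ICC is an assumption.

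| ICC | DE | Power, 21 per group | Power, 36 per group |
|---|---|---|---|
| 0 | 1.0 | .992 | .992 |
| .05 | 1.2 | .975 | .975 |
| .10 | 1.4 | .948 | .948 |
| .15 | 1.6 | .912 | .912 |

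**4. Power at planned enrolment.** After 10% drop-out about 43, 43 and 22 children remain, or 4.5 per group, so DE = 1 + 3.5 × ICC. In this calculation the plan's f corresponds to a standardized difference in change of 4f, that is 1.6 and 1.2. Noncentrality is 1.6 × √(43 × 22/65) = 6.10 and 1.2 × √(43 × 43/86) = 5.56, each divided by √DE. Two-sided critical t at .01 is 3.01 on 13 df and 2.88 on 18 df, against about 2.65 on child-level df.

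| ICC | DE | SST vs care-as-usual | SST vs SST-PTI |
|---|---|---|---|
| .05 | 1.175 | .989 | .980 |
| .10 | 1.350 | .976 | .960 |
| .15 | 1.525 | .956 | .933 |

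**5. Type I error if the group is left out.** A child-level t-test at nominal .01 was simulated with 10 against 5 groups.
- Same ICC in both arms: about .018 (ICC .05), .029 (.10) and .045 (.15).
- No correlation in care-as-usual: from about .013 (ICC .05) to .018 (.15).

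Rough check at equal ICC .10: 2.656/√1.4 = 2.245, a two-sided tail of about .025. The simulated value is a little higher.

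**The case against.** The strongest objection is to the analysis half. Hierarchical and multilevel models can hold children within training groups, the section excludes no level, and a condensed article commonly leaves random effects to the full plan. This stands. A reader might infer that the trial will ignore its groups, but the document does not say so, and the type I error figures apply only if it does.

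Second, care-as-usual children receive no SST and share no sessions, so their correlation may be well below that in the training arms. This also stands, and it is why the type I error is given as a range. Some correlation from shared location and recruitment period may remain. Including location in the model could absorb part of it.

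Third, the loss of power is modest. Enrolling 48 rather than 40 per training arm absorbs part of it, and the ICC of a parent-interview change score measured six months after training could be below .05. At ICC .01 and groups of 5, power at the minimum sizes is still .989. This limits the size of the point, but does not make the printed calculation one for this design.

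A reader might also infer that clustering leaves the trial badly underpowered. If 0.90 and 0.60 SD are read as differences in change, cluster-df power is about .57 and .41 at ICC .05. On that reading it is already about .66 and .48 at ICC 0, so most of the shortfall comes from how the SD differences were turned into f. That is a separate matter and is not counted here.

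**Conclusion.** The point holds. The Sample size calculation section prints a calculation for independently randomized children, while the Randomization section describes groups, so the .99 power is not supported as stated. Over an assumed ICC of .05–.15, power falls to about .975–.912 at the stated minimum sizes. At planned enrolment it is about .989–.956 for SST against care-as-usual and .980–.933 for SST against SST-PTI. These figures take the plan's own f values, groups of 5 and roughly 10, 10 and 5 groups. On those terms the trial remains well powered.

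The more consequential part is conditional. The analysis wording leaves open whether the randomized group enters the model. If it does not, a nominal .01 primary test could run from slightly above its level to more than four times it (.013 to .045). With only 4–6 care-as-usual groups, the degrees of freedom matter as well as the random effect.

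**What to change.** - **Statistical analyses.** State that the randomized group is a level of every efficacy model, with child and time below it. The random effect should act on change (a group effect on change, or group-by-time). A group intercept that is constant over time cancels from a T3–T1 contrast and would not protect it. Use small-sample degrees of freedom, such as Kenward-Roger or Satterthwaite, and report the estimated ICC.
- **Sample size calculation.** Restate the power over an ICC range, using the actual number of groups per arm.
- **Strengths and limitations.** Reconcile the description of random assignment with the Randomization section.

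The cost is small. The Trial status section says that all participants have been randomized and that the last T3 assessments are still to come, so the model can be fixed before the final analysis. Enrolment does not change, and group membership is known from the allocation. The price is somewhat wider intervals and a slightly lower stated power.

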### Intervention

#### Social skills training

The manualized SST consists of 15 weekly sessions (except for school vacations), followed by three booster sessions starting two months after the 15^th^ session. An SST group consists of four to six children and two therapists. Each session lasts 90 minutes and is video-taped. The SST is based on behavioral therapeutic principles and the social learning theory. The purpose of the SST for children is to learn to interact with other children and to experience that interacting with other children can be fun. Children are taught through instruction, directed positive feedback, observation, and role-play. The therapists analyze the behavior of the children, define individual positive target behaviors, and elicit positive behavior. Negative behavior is ignored when possible, while differentially reinforcing alternative or incompatible positive behavior.

As shown in Table 2, in sessions 1 to 4, the first phase of the SST, the most important aim is to create a safe environment for the children to practice. In sessions 5 to 15, the second phase, nine skills are discussed, practiced, and rehearsed, for instance ‘asking something to someone’, or ‘apologizing to someone’. Sessions 16 to 18 are the so called booster sessions, in which the most relevant skills for each individual child are rehearsed.

**Table 2 T2:** Topics of the social skills training

** *Children sessions (in SST and SST-PTI)* **		
**1**	Phase 1 (weekly): Create a safe environment	Introduction
**2**		Saying nice things about yourself and to others
**3**		Feelings (showing how you feel and see how another feels)
**4**		Personal presentation (posture, eye contact and use of voice)
**5**	Phase 2 (weekly): Practice skills	Asking something to someone
**6**		Conversation
**7**		Asking for a play date
**8**		Asking to participate
**9**		Discussing with someone
**10**		Playing a social game
**11**		Saying no
**12**		Indicating annoyance
**13**		Apologizing to someone
**14**		Responding to bullying
**15**		Final session, children chose a social activity
**16**	Phase 3 (2 weekly-monthly): Booster sessions	Repeating the above mentioned skills, focusing on individual goals
**17**		Repeating the above mentioned skills, focusing on individual goals
**18**		Repeating the above mentioned skills, focusing on individual goals
** *Parents sessions (in SST-PTI)* **		
**1**	Phase 1 (weekly): Before child sessions	Psycho-education
**2**		Antecedent interventions
**3**		Consequent interventions
**4 (SST 2)**	Phase 2 (2 weekly): During child sessions	Discrimination training
**5 (SST 4)**		Eliciting desired behaviors and creating opportunities
**6 (SST 6)**		Energizing desired social behavior
**7 (SST 8)**		Responding to and redirecting socially awkward behaviour
**8 (SST 11)**	Phase 3	Continuation and persevere
** *Teacher (in SST-PTI)* **		
**1**	One meeting with the therapist before the start of the SST for the children en five telephone contacts during the SST (after session 2, 4, 7, 10 and 13).	

Before the start of the training, one of the therapists meets with the child and his/her parents in order to get to know each other and to give practical information. Additionally, this meeting serves as the moment for determining five individual goals of the participant. The parents, child, and therapist together choose five specific behaviors that the child and therapist will focus on during the training.

In order to evaluate the training, the child, parents, and therapists meet and discuss the training and learned skills after the fifteenth session. After the booster sessions, the therapists call the parents for a final evaluation.

For children in this condition, only medication is allowed as an additional treatment.

#### Social skills training – parent & teacher involvement

In the SST-PTI condition, each child follows the exact same procedure as described above for the SST condition. Additionally, his/her parent(s) participate in eight parent sessions. Preferably, both parents participated, however, in many cases only one parent was able or willing to participate. Another addition is that the teacher is coached to support the child in school. An overview of the parent sessions and teacher involvement is presented in Table 2.

The parent sessions are directly linked to the SST sessions and focus on how to support and assist the child in performing the social skills as learned in the training. The sessions consist of instruction on and explanation of behavioral therapeutic principles, behavioral exercises, role-play, and homework. Three parent sessions take place before the children’s SST sessions start. In these sessions, antecedent and consequent interventions are discussed. The parent(s) learn to distinguish desirable social behavior from undesirable social behavior and to elicit the desirable behavior. The other five sessions take place at determined moments during the SST and these are focused on how to support their child in learning and practicing social skills, based on the parental skills from the first three sessions.

Before the children start with their SST sessions, the teacher has one meeting with the therapists concerning (further) education on ASDs, explanation of the SST and specific behavioral instructions. The teachers receive a file with all child sessions and the weekly homework. Additionally, one of the therapists is in contact with the teacher five times throughout the 15 weeks that the child participates in the SST sessions, in order to discuss the possibilities for practicing the weekly homework skills in school and the individual goals.

Also for children in this condition, only medication is allowed as an additional treatment.

#### Care-as-usual

Children in the care-as-usual condition receive no SST. Medication, parent training, and other treatments are allowed and content, frequency, and duration are registered by the researchers. However, parents or child do not receive psychological interventions primarily focusing on improving social skills. Participants in the care-as-usual condition can take part in an SST after the follow-up assessment, one year after start of the SST in the treatment conditions.

### Assessments

Assessments were planned at three moments: before randomization, immediately after the intervention period, and at 6 months follow-up after the end of intervention. The first assessment (T1) was planned after inclusion of the child and the decision of parents and child to participate. This assessment comprises questionnaires for children, parents, and teachers, interviews with parents, and observations of children. Six months later (after SST session 15) the second assessment (T2) was planned, including questionnaires for parents, child, and teacher, an interview with parents, and observations of the child. Another six months later the follow-up (T3) was planned, with all instruments included at T2 for parents and child. No teacher information was going to be collected at this point, since children often have a different teacher on T3 than on T1 and T2 (due to change of class in the end of the school year). In the care as usual condition, T2 was planned six months after T1 and T3 twelve months after T1. Currently, T1 and T2 have been completed. The last group will complete T3 in the summer of 2014.

